##### Implementation {16c}

The participating surgeons (PI or Co-Is) and appropriate research personnel are responsible for enrollment during the preoperative clinic evaluation. A study coordinator and/or a research fellow is responsible for generating the allocation sequence intraoperatively per surgeon request after crural reapproximation.

#### Assignment of interventions: blinding

##### Who will be blinded {17a}

Patients are under general anesthesia when allocation assignments are distributed and thus blinded to their assigned intervention. Patients will remain blinded until their participation in the study is complete. The operating surgeons are unblinded to the allocation arm. However, patients are not randomized until crural closure is complete, thus limiting surgeon bias and technical variations of the procedure up to this point. Outcome assessors are blinded to the patients’ allocation arm when evaluating 30-day and 1-year follow-up data.

##### Procedure for unblinding if needed {17b}

Circumstances in which unblinding is permissible would be in the event of a postoperative surgical emergency that required revision of the recent paraesophageal hernia repair. The surgeon may disclose operative findings and events to the patient per their discretion.

#### Data collection and management

##### Plans for assessment and collection of outcomes {18a}

An UGI or CT scan will be used at the 1-year follow-up period to assess for radiographic hiatal hernia recurrence. Three surgeons will serve as the blinded assessors for this study and will complete training on the definition of PEH recurrence per the protocol. Agreement must be reached between at least two of them to be accepted as the consensus. GERD-HRQL, a validated 11-item instrument, will be used to assess GERD, dysphagia, odynophagia, and gas bloat symptoms as well as patient satisfaction at the 30-day and 1-year follow-up periods [26]. Additionally, numeric rating scales, which have been used in prior PEHR research [19, 22, 23], will be used to evaluate regurgitation, chest pain, abdominal pain, nausea, vomiting, postprandial pain, cardiovascular, and pulmonary symptoms at the 30-day and 1-year follow-up periods.

##### Plans to promote participant retention and complete follow-up {18b}

Patients will be scheduled for a postoperative clinic appointment within the 30-day and 1-year follow-up periods, both of which are our routine standard of care. Implementing 1-year radiographic follow-up will be the most challenging aspect of the trial. Several mechanisms have been established to promote patient retention and follow-up completion. The 30-day follow-up period will extend from 15 to 45 days postoperatively, and the 1-year follow-up period will extend from 6 to 18 months postoperatively. Appointment reminders will be sent via patient online portals and nursing phone calls. Virtual follow-up visits can be accommodated and patients can complete UGI or CT scans at their local institutions, provided the imaging can be uploaded into CCF’s digital platform for review. For patients who have missed follow-up appointments, the dedicated study coordinator, research fellow, and/or surgeon will call patients to reschedule or send the GERD-HRQL and numeric rating scales by mail to collect this information. This will increase convenience for patients and protocol adherence. Appropriate statistical analyses will be conducted to account for missing data.

##### Data management {19}

The DDSI-QC will serve as the platform for data collection, including baseline, follow-up, and outcomes data. It will also capture granular operative details. The DDSI-QC is an enterprise-wide quality improvement effort hosted at the Cleveland Clinic Foundation in the form of a database featuring prospectively collected, point-of-care, surgeon-entered data.

##### Confidentiality {27}

Subject anonymity and data confidentiality will be maintained before, during, and after the trial period. Every effort will be made to maintain the confidentiality of documents that identify the subject by name (e.g., signed informed consent documents, clinic charts), except to the extent necessary to allow monitoring by the Office of Research Compliance at the Cleveland Clinic or by other regulatory authorities.

The information collected will be stored in the DDSI-QC, a secure institutional database that is used to track clinical outcomes in patients who undergo operations by surgeons in CCF’s DDSI. Written consent forms and data collection forms will be stored in binders, which will stay in a locked office in the Crile Building at CCF. Randomization will occur with the use of a customized REDCap®, a secure network/firewall-protected electronic database to which only the investigator and the designated members of the study team will have access using an individually assigned login and password. Only approved study members listed on the Institutional Review Board (IRB) protocol will have access to the separately stored master list—which will be stored in a Cleveland Clinic password-protected computer and saved on an S drive. Only the Principal Investigator, lead research coordinators, and biostatisticians will be granted access to retrieve patient data for data quality assessment and data analysis. All electronic records pertaining to the clinical study will be password-protected and only approved study members listed on the IRB protocol will have password access.

##### Plans for collection, laboratory evaluation, and storage of biological specimens for genetic or molecular analysis in this trial/future use {33}

Not applicable. No biologic specimens will be collected during the study.

#### Statistical methods

##### Statistical methods for primary and secondary outcomes {20a}

All analyses will be performed using the intent-to-treat population and will be done under the normality assumption, if appropriate. Patient characteristics will be summarized overall and by randomized group, and differences will be described as standardized effects. All tests will be considered significant at 5% level. Outliers for each endpoint will be assessed with a graphical method, such as the box plot. All primary and secondary endpoints will be initially evaluated using all observations and then evaluated with a sensitivity analysis without including points identified as outliers. All statistical analyses will be performed with SAS software (version 9.4; Cary, NA) or R software (version 4.0.0, 2020-04-24; Vienna, Austria).

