### Objectives {7}

The primary objective of this trial is to investigate the rates of radiographic PEH recurrence at 1 year in patients receiving anterior gastropexy compared to those receiving no anterior gastropexy during minimally invasive PEHR. The cumulative recurrence rates for laparoscopic PEHR with anterior gastropexy ranges from 0 to 25% [12, 15–20], compared to the recurrence rates without anterior gastropexy ranging from 7 to 66% [3, 16, 21–24]. This data is limited by variable lengths of follow-up and definitions of recurrences. We hypothesize that anterior gastropexy will result in a 15% reduction in PEH recurrence after minimally invasive repair compared to no gastropexy. Based on previously published data and our group consensus, we feel that a 15% reduction is a conservative but clinically important difference that supports the routine use of anterior gastropexy during PEHR.

Secondary objectives include the rates of symptomatic gastroesophageal reflux disease (GERD), dysphagia, odynophagia, gas bloat, regurgitation, chest pain, abdominal pain, nausea, vomiting, postprandial pain, cardiovascular, and pulmonary symptoms as well as patient satisfaction in the immediate postoperative and 1-year follow-up periods between the two groups.

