##### Secondary outcomes

Secondary outcomes include patient-reported symptoms of GERD, dysphagia, odynophagia, gas bloat, regurgitation, chest pain, abdominal pain, nausea, vomiting, postprandial pain, cardiovascular, and pulmonary complaints along with patient satisfaction from GERD-HRQL and the numeric rating scale measured at baseline, 30 days postoperatively, and 1 year postoperatively. Generalized linear mixed effect models will be used to compare categorical outcomes, and linear mixed effect models will be used to compare numeric continuous score outcomes. In these models, groups will be analyzed using fixed effect parameters and surgeons will be analyzed using random effect parameters.

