### Methods for additional analyses (e.g., subgroup analyses) {20b}

A priori defined exploratory analyses will be performed to evaluate the effects of fundoplication on symptoms of GERD, dysphagia, regurgitation, and chest and abdominal pain. For patients with PEH recurrence, the differences in symptoms of those with a fundoplication will be compared to those without a fundoplication as another exploratory endpoint. Our a priori hypothesis is that a recurrent hiatal hernia with a fundoplication in the mediastinum is more symptomatic for patients than recurrences without a fundoplication in the mediastinum. Differences between groups will be tested and described as standardized effects using chi-square test or Fisher’s exact test for binary variables and Student’s *t* test or Wilcoxon rank sum test for continuous variables with a 95% confidence interval and a *P* value of <0.05 denoting statistical significance.

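### Every test, including those on 13 patient-reported secondary outcomes, is declared significant at 5% with no hierarchy, correction or supportive label, so the chance of some false secondary claim is well above 5%

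*Protocol article*

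**What the plan says.** - **Level.** Section {20a}, whose heading covers both primary and secondary outcomes, sets one rule: "All tests will be considered significant at 5% level".
- **Outcomes.** The Secondary outcomes paragraph of the statistical methods lists "symptoms of GERD, dysphagia, odynophagia, gas bloat, regurgitation, chest pain, abdominal pain, nausea, vomiting, postprandial pain, cardiovascular, and pulmonary complaints along with patient satisfaction", which is 12 symptoms plus satisfaction, "measured at baseline, 30 days postoperatively, and 1 year postoperatively".
- **Comparison.** Objectives {7} makes the between-arm comparison of the symptoms a secondary objective, "as well as patient satisfaction in the immediate postoperative and 1-year follow-up periods between the two groups".
- **Method.** The same paragraph assigns mixed models to both the categorical outcomes and the numeric scores. On their structure it says only this: "groups will be analyzed using fixed effect parameters and surgeons will be analyzed using random effect parameters". No group-by-time term and no contrast at a particular visit is stated.
- **Labels.** The word exploratory is kept for a different set of analyses: "A priori defined exploratory analyses will be performed to evaluate the effects of fundoplication on symptoms" (section {20b}, where P below 0.05 is again the criterion). The randomised symptom comparisons carry no such label.

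No section names a key secondary outcome, a testing order, a gate on the primary result or a multiplicity correction.

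**The concern.** Had the protocol said nothing about multiplicity among the secondary outcomes, that could be left to an analysis plan that is not shown. Here it fixes a rule, and the rule gives a symptom result at P below 0.05 the same declared status as the result for radiographic recurrence. With 13 outcomes and no structure, some false declaration of a symptom benefit or harm can arise by chance far more often than the stated 5% suggests. Such a result would draw most attention if the recurrence comparison were neutral. At stake is how the secondary results may be described. The validity of the primary test is not in question.

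**Working it through.** **1. The plan's own figure.** The protocol gives no family-wise error figure for the secondary outcomes. The one figure tied to the 5% level is the sample size in Sample size {14}: control recurrence 0.24, a reduction of 15% (read as 15 percentage points, so 0.09), two-sided 5%, at least 80% power, 20% loss.

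n per arm = [1.96 × √(2 × 0.165 × 0.835) + 0.842 × √(0.24 × 0.76 + 0.09 × 0.91)]² / 0.15² = [1.029 + 0.433]² / 0.0225 ≈ 95.

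The total is 190 evaluable, and 190 / 0.8 = 237.5, so 238, against the stated 240. With 120 × 0.8 = 96 evaluable per arm, power is 80.4%. The figure is reproduced. It uses one test at 5%, so nothing below changes it.

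**2. Number of secondary tests, m.**
- One group effect per outcome: m = 13.
- Each outcome tested separately at the two post-operative times: m = 13 × 2 = 26.

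The Objectives name both periods, but the model description states only a group effect. Both counts are therefore open.

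**3. Independent tests, no true effect on any outcome.** The chance of at least one false positive is 1 − (1 − 0.05)^m.
- m = 13: 1 − 0.95^13 = 48.7%; expected number of false positives 13 × 0.05 = 0.65.
- m = 26: 1 − 0.95^26 = 73.6%; expected number 26 × 0.05 = 1.3.

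The expected numbers hold whatever the correlation.

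**4. Correlated tests.** Symptom scores in the same patients will be correlated, and the protocol gives no value. The figures below come from 200,000 simulated sets of standard-normal test statistics with a common correlation and a two-sided critical value of 1.96. Two-sided testing is taken from the sample-size section, since {20a} does not state it.

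| Assumed correlation | 13 tests | 26 tests |
|---|---|---|
| 0 | 48.6% | 73.6% |
| 0.3 | 41.8% | 61.7% |
| 0.5 | 33.3% | 47.6% |
| 0.7 | 24.1% | 32.2% |
| 0.8 | 19.1% | 24.4% |

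If the correlation is 0.5 between symptoms and 0.5 between times (0.25 across both), 26 tests give about 53%.

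**5. Against the stated level.** The lowest entry is 19.1 / 5 = 3.8 times 5%; the highest is 73.6 / 5 = 14.7 times.

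**The case against.** The strongest reply is that this is ordinary practice. There is one primary objective, one primary outcome and a sample size built on it, and the symptoms are called secondary throughout. Many trials report unadjusted secondary tests beside a single primary. The article is condensed, and handling of multiplicity is often left to the analysis plan. The 5% sentence may be only a general convention, and the proposed relabelling changes no number.

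Much of this stands, and it limits the point to a wording change. It does not remove it. Unadjusted secondary tests are defensible when they are called supportive; this text declares them significant and uses a weaker label only for the fundoplication analyses.

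The count is also open to challenge. GERD, dysphagia, odynophagia and gas bloat all come from one 11-item instrument. If that yielded a single symptom score, there would be 10 outcomes: that score, satisfaction and eight rating scales. Then 1 − 0.95^10 = 40% if independent, and about 29% at correlation 0.5. The size shrinks, but it stays well above 5%.

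Three stronger readings are tempting, and the protocol does not support them:
- **A false symptom finding is more likely than not.** That needs 26 tests and low to moderate correlation. With 13 tests no scenario reaches one half, and the protocol does not state separate tests at each visit.
- **A chance symptom result could lead to the procedure being abandoned.** The Discussion makes abandonment conditional on gastropexy proving ineffective. The discomfort it mentions is at the points where the sutures cross the fascia, which is not one of the 13 outcomes. Nothing ties a decision to a symptom P value.
- **Morbidity, length of stay, readmission and the complication indices add further tests.** They are collected, but no between-arm test is stated for them and the statistical section does not list them among the secondary outcomes.

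**Conclusion.** The point holds for the secondary outcomes only. As written, the plan allows any of the 13 patient-reported outcomes to be declared significant at 5%. With no true effect on any of them, the chance of at least one such declaration is about 19% to 49% for 13 tests and about 24% to 74% for 26. These ranges rest on an assumed common correlation between 0.8 and 0, and on two-sided tests that each hold their nominal 5%. The protocol fixes neither the correlation nor the number of contrasts, so no single figure should be quoted as the trial's error rate. The primary endpoint's 5% level, its power and N = 240 are unaffected. This is a cheap improvement to make before the analysis, and it does not threaten the trial's main conclusion.

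**What to change.** In section {20a}, replace the sentence on the 5% level with wording such as:

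> The primary endpoint is tested at the two-sided 5% level. All secondary comparisons are supportive. They are reported as estimates with 95% confidence intervals that are not adjusted for multiplicity, and no claim of statistical significance is made from them.

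Optionally, if the sponsor wants one confirmatory symptom claim, it can name one secondary outcome at one time point in advance and test it at 5% only if the primary is significant. The rest stay supportive.

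The change needs no extra patients, visits or data and leaves the primary analysis as it is. The cost is that individual symptom differences can no longer be called statistically significant.

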##### Primary outcome

The primary endpoint of this study is radiographic recurrence rates at 1 year following either anterior gastropexy (intervention) or no anterior gastropexy (control) during paraesophageal hernia repair. Differences between the two groups will be tested and described using a binomial regression model with identity link and robust variance estimation. Pre-specified covariates will include fundoplication vs. no fundoplication, Type II/III vs. Type IV PEH, body mass index (BMI), sex, and surgeon, with the surgeons modeled as cluster effect. Results will be presented as relative risk and absolute risk differences with a 95% confidence interval. In cases where the model fails to run due to convergence issues, a Poisson GEE model with robust variance estimates, a log Poisson regression model, or a linear regression GEE model with exchangeable correlation and robust standard errors will be used to estimate the risk difference.

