### Eligibility criteria {10}

The study population includes adult patients (≥ 18 years) undergoing elective, minimally invasive repair of a symptomatic, primary paraesophageal hernia measuring at least 5 cm in height on computed tomography (CT), upper gastrointestinal series (UGI), or endoscopy, where the diaphragmatic crura can be primarily reapproximated at the time of surgery without the use of mesh using either a laparoscopic or robotic approach. Only patients who are able to participate in follow-up and consent to participate will be included. Patients whose operations begin with a minimally invasive approach and are converted to open will be included provided that they meet all other criteria. The technique for crural closure and the use or avoidance of a fundoplication are both left to the discretion of the surgeon.

Exclusion criteria include patients who are not eligible for a minimally invasive repair or have undergone prior esophageal or gastric operations, including hiatal hernia repair, cruroplasty, esophageal lengthening procedures, esophagectomy, or any prior gastric resections. However, patients who have previously undergone gastrostomy tube placement alone will remain eligible for inclusion. Additional exclusion criteria include patients undergoing PEHR with a concurrent bariatric procedure (sleeve gastrectomy, Roux-en-Y gastric bypass, duodenal switch, single-anastomosis gastric bypass, and total gastrectomy), as well as patients undergoing PEHR with concomitant placement of a gastrostomy tube. If the surgeon feels mesh is necessary to augment hiatal closure at the time of operation or if a Collis gastroplasty is required for esophageal length, these patients will also be excluded. Reasons for patient exclusions from the trial will be documented and reported in the Consort diagram.

Surgeon eligibility requires fellowship training with expertise in minimally invasive PEHR. All participating surgeons are also required to undergo training to ensure understanding of the protocol and technical aspects of performing the anterior gastropexy as described in the protocol.

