### Outcomes {12}

#### Primary outcome

The primary outcome of interest is radiographic paraesophageal hernia recurrence at 1 year postoperatively in patients receiving anterior gastropexy compared to those receiving no anterior gastropexy. An upper gastrointestinal series (UGI) or computed tomography (CT) scan will be obtained at the 1-year follow-up visit as per standard of care at our institution. Imaging obtained within the CCF system and at other institutions at the 1-year time point will be eligible for review provided that these are uploaded into Epic. Imaging will be reviewed by outcome assessors who are blinded to the treatment group and a consensus among assessors is required. A height of 2 cm of stomach, fundoplication or other abdominal organ (excluding the esophagus) above the diaphragm will constitute a radiographic recurrence, as previously described by Oelschlager et al. [25]. Herniation < 2 cm will not be considered a recurrence for the purposes of this study. Additionally, the need for reoperation secondary to fundoplication disruption, dysfunction, or slippage at any time during the study period will be considered a recurrence. We hypothesize that recurrence rates at 1 year after surgery for patients who receive anterior gastropexy will be decreased by 15% or more compared to those receiving no anterior gastropexy.

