### Sample size {14}

Assuming a 20% rate of loss to follow-up, enrollment of 240 participants with 120 participants in each arm will provide at least 80% power for showing superiority of anterior gastropexy to no anterior gastropexy for the primary endpoint of decreased recurrence rates by 15% at the 1-year postoperative visit using a two-sided chi-square test and an alpha level of 5%. For the purpose of calculating the power of this study, the proportion of recurrences in the control group (no anterior gastropexy) is estimated to be 0.24. This is based on the reported recurrence rates for paraesophageal hernia repair without gastropexy, ranging from 7 to 66% [3, 16, 21–24], with the majority falling between 13 and 42% [3, 16, 23, 24] at various time points after surgery.

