#### Assignment of interventions: allocation

##### Sequence generation {16a}

This is a two-armed trial with an allocation ratio of 1:1 between the control (no anterior gastropexy) and intervention (anterior gastropexy) arms. Patients are randomized using a computer-generated random allocation sequence. The random allocation sequence was built using a Research Electronic Data Capture (RedCAP®) database hosted at Cleveland Clinic Main Campus in Cleveland, Ohio. A randomization allocation table has been generated and uploaded into REDCap® by a CCF statistician. No planned restrictions will be included. Both institutions involved in this study will use the same randomization allocation sequence that is hosted at Cleveland Clinic Main Campus in Cleveland, Ohio.

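### The primary model leaves out preoperative hernia height, an available and plausibly prognostic covariate, and so may give up a modest amount of precision

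*Protocol article*

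**What the plan says.** - **Eligibility criteria {10}** admits patients with a "primary paraesophageal hernia measuring at least 5 cm in height on computed tomography (CT), upper gastrointestinal series (UGI), or endoscopy". A height must therefore be established before surgery.
- **Outcomes {12}, Primary outcome** defines the radiographic part of the endpoint: "A height of 2 cm of stomach, fundoplication or other abdominal organ (excluding the esophagus) above the diaphragm will constitute a radiographic recurrence". Reoperation for certain fundoplication failures also counts as recurrence, so the endpoint is a yes/no composite.
- **Sequence generation {16a}** describes 1:1 allocation and adds "No planned restrictions will be included".
- **Statistical methods, Primary outcome** specifies an identity-link binomial model with robust variance and surgeons as clusters. The covariate list is: "Pre-specified covariates will include fundoplication vs. no fundoplication, Type II/III vs. Type IV PEH, body mass index (BMI), sex, and surgeon". Height is not on it, and no reason is given.
- **Sample size {14}** says that 240 patients "will provide at least 80% power for showing superiority", with "the proportion of recurrences in the control group (no anterior gastropexy) is estimated to be 0.24" and 20% loss to follow-up.

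**The concern.** The protocol commits to an adjusted primary analysis and names its covariates, so the list is a choice open to comment and not a detail left to a later document. The only descriptor of hernia extent on the list is Type II/III against Type IV. All Type II and III hernias, from 5 cm upward, are treated alike. The one continuous preoperative measure of size goes unused, although it is on the same physical scale as the radiographic criterion. By contrast, fundoplication is adjusted for even though the Discussion says it is not expected to confound the endpoint.

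Two things are at stake. If height predicts recurrence, adjusting for it narrows the confidence interval without extra patients, in a trial planned close to its 80% power floor. And because allocation is unrestricted, the arms may differ in hernia size by chance. A visible imbalance would invite an unplanned adjustment after the fact, which pre-specification avoids.

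**Working it through.** **1. Reproduce the planned sample size.** Inputs from Sample size {14}: control risk 0.24; a 15% decrease read as absolute, so 0.09 with gastropexy; two-sided alpha 0.05; power 0.80; 20% loss. With mean risk 0.165 and no continuity correction:

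n = [1.96·√(2·0.165·0.835) + 0.842·√(0.24·0.76 + 0.09·0.91)]² / 0.15² = (1.029 + 0.433)² / 0.0225 ≈ 94.9, so 95 per arm.

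95 / 0.8 = 118.75, so 119 per arm and 238 in total, against the stated 240. A relative 15% reduction (0.24 against 0.204) would need 2,091 evaluable per arm, so the absolute reading is the one used.

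**2. Baseline power.** With 120 × 0.8 = 96 evaluable per arm, the pooled chi-square calculation gives 80.4%. With the unpooled standard error, √[(0.1824 + 0.0819)/96] = 0.0525, it is 81.6%. The simulations below use robust standard errors, so they start near the second figure.

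**3. Gain from adding height.** The prognostic strength of height is not in the protocol and is assumed: odds ratio (OR) 1.0 to 2.5 per SD, height standardised and normally distributed. R² is the share of within-arm outcome variance explained by height, pooled over arms; variance is multiplied by about 1 − R², and the equivalent extra patients per arm are 96/(1 − R²) − 96. Power is from 20,000 simulated trials per row, 96 per arm, using a linear risk-difference model with robust standard errors and none of the listed covariates.

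| OR per SD | R² | Simulated variance ratio | Power without height | Power with height | Equivalent extra patients per arm |
|---|---|---|---|---|---|
| 1.0 | 0 | 1.006 | 81.6% | 81.6% | 0 |
| 1.5 | 0.021 | 0.981 | 81.9% | 82.8% | 2 |
| 2.0 | 0.055 | 0.954 | 81.5% | 83.5% | 6 |
| 2.5 | 0.088 | 0.910 | 81.7% | 85.2% | 9 |

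**4. Against a model that already holds hernia type.** The fairer comparison is type alone against type plus height. Simulated that way, the gain is roughly 0.3 to 3.5 points for ORs of 1.5 to 2.5, with variance down about 1 to 9%. The low end arises where type and height overlap.

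**5. Under the missing-data rule.** Section {20c} counts patients lost to follow-up as non-recurrent and keeps 240 as the denominator. With 20% loss in each arm the risks become 0.24 × 0.8 = 19.2% and 0.09 × 0.8 = 7.2% of 120 per arm, and pooled chi-square power is about 79%. The gain from height stays within the range in step 4.

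**6. Chance imbalance.** With 96 per arm, one standard error of the difference in mean height is √(2/96) = 0.144 SD. The slopes in risk per SD of height are 0.0522, 0.0853 and 0.1077 for ORs of 1.5, 2.0 and 2.5. A 1-SE imbalance therefore shifts the unadjusted risk difference by 0.8, 1.2 or 1.6 points, and a 1.96-SE imbalance by 1.5, 2.4 or 3.1 points, against a 15-point target.

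**The case against.** The strongest reply is that the plan already pre-specifies a sensible adjusted model with an anatomical severity term, that nothing in it is misstated, and that one more covariate is a matter of preference. Several parts of that reply stand.

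- **Height is not the baseline value of the outcome.** A reader might infer that it is, since both are measured in centimetres above the diaphragm. The protocol does not support this. The endpoint is a binary composite that includes some reoperations, and the operation reduces the hernia in between. Height is a candidate prognostic factor only, and the protocol does not say that it predicts recurrence.
- **A large gain is not realistic.** Applying a correlation of 0.5, as one might for a continuous outcome, takes power from about 82% to 91%. For a binary outcome at 24% risk that correlation needs an OR above 4.5 per SD; at 9% risk, even an OR of 20 gives only 0.48.
- **The planned covariates matter.** The table in step 3 compares with no adjustment at all. Step 4 allows for hernia type, but not for BMI, sex, fundoplication or surgeon.
- **There are costs.** About 32 events are expected (96 × 0.24 ≈ 23 plus 96 × 0.09 ≈ 9). Another continuous term slightly raises a convergence risk that the plan already anticipates, and three imaging modalities add measurement noise. Table 1 does not name hernia size as an assessment, so recording it needs a transcription step.

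These points shrink the benefit without removing it. Neither type in the model nor the missing-data rule reverses the direction, and essentially nothing is lost if height is not prognostic.

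**Conclusion.** The point holds as a modest improvement in efficiency. Height is required for eligibility, is absent from the named covariates and is not balanced by the design. For assumed ORs of 1.5 to 2.5 per SD, including it lowers the variance of the risk difference by about 1 to 9% and adds up to about 3.5 points of power, towards the lower end where hernia type already carries size information. With no association the gain is zero. The range rests on an assumed prognostic strength, a normally distributed height and the planning risks of 24% and 9%. Truncation at 5 cm and mixed modalities would tend to reduce it.

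A reader might go further and infer that the omission biases the primary comparison or undermines the sample size. It does neither. Randomisation keeps the estimate unbiased on average, the confidence interval already allows for chance imbalance, the type I error rate is unaffected, and the planned 240 reproduces.

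**What to change.** Before unblinding, in Statistical methods, Primary outcome, add preoperative hernia height (cm, continuous, from the eligibility imaging) to the pre-specified covariates, and fix the order in which CT, UGI and endoscopy values are used when more than one exists. Transcribe the eligibility value into the baseline record of the registry for every randomised patient. If the identity-link model does not converge, use the fallback models that the section already lists, keeping the surgeon clustering. If the investigators prefer to leave height out, a sentence giving the reason would do.

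The cost is one sentence and one transcribed field, with no new imaging, visit or patient, plus the extra parameter, convergence risk and measurement noise noted above. Measurement noise reduces the gain but does not bias the randomised comparison.
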